##### Opinion scale

This 8-item instrument was developed specifically for this trial in order to get more feedback about the participants’ opinions about TAO. Four of the items are answered using an 11-point response scale, rating different statements from 0 (“Not at all”) to 10 (“Very much”): (1) usefulness; (2) attractiveness; (3) convenience; (4) recommendation. Then, four short-answer questions are included to collect qualitative data about: (1) the most useful module; (2) positive features of the intervention; (3) negative features of the intervention; and (4) the overall opinion. This scale will be filled out at post-intervention.

#### Suicidal risk

The presence, frequency, and severity of suicidal thoughts will be assessed during the *Diagnostic Interview for Adjustment Disorders* administered by phone. The inclusion of a suicide item after each program module, at post-intervention, and at follow-up assessments will make it possible to detect participants who are at risk of suicide during the intervention and once the intervention is over.

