### Study groups

#### Adjustment disorders online (TAO)

Adjustment Disorders Online (TAO) is an ICBT based on a manualized protocol for the treatment of AjD, structured in a therapist handbook and a patient handbook. TAO comprises the following therapeutic components: psychoeducation, techniques to manage negative emotions, exposure, problem-solving techniques, mindfulness, acceptance and elaboration of the stressful event, positive psychology strategies, and relapse prevention. It is the optimized version of the original intervention protocol for AjD developed by Botella et al. [31]. More specifically, TAO also includes behavioral activation for mood disturbance, problem-solving techniques to improve the capacity to deal with everyday challenges, and mindfulness to become aware of the thoughts and feelings related to the stressful event instead of trying to escape from them.

The intervention is easily accessible over the internet at https://www.psicologiaytecnologia.com/. In order to provide a more enjoyable experience, the program content is presented through texts, videos, pictures, vignettes, and interactive exercises. Different contents can also be downloaded as PDF files so that users can review them offline.

TAO is organized into seven sequential modules (see Table 1), and it takes about 7 to 10 weeks to complete it. Although users are encouraged to advance one module per week, some modules may require more time. Therefore, the program also emphasizes that everyone should progress at their own pace, dedicating enough time to understand the module contents and carry out the proposed activities.

**Table 1 Tab1:** TAO content

Module	Aims of the module	Contents
0. Welcome module: starting this program.	- Providing information about TAO. - Promoting the adherence to the program. - Enhancing motivation for change.	- Information about the contents of each module. - Recommendations to get the maximum benefit from the program. - Meditation on reasons to change. - Goal setting.
1. Understanding emotional reactions.	- Providing information about AjD and common reactions to stressful events. - Learning of strategies to manage negative emotions.	- Psychoeducation. - Behavior activation. - Slow breathing technique.
2. Learning to deal with negative emotions.	- Facing avoided situations that contribute to the maintenance of the problem. - Improving the ability to deal with everyday challenges.	- Exposure. - Problem solving technique.

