3. Accepting problems.	- Becoming aware of the personal experiences related to the stressful event. - Elaborating and processing the stressful event through the acceptance of the problematic situation.	- Mindfulness. - The Book of Life: Acceptance. - Elaboration of a metaphorical meaning for the stressful event.
4. Learning form problems.	- Starting to see problems as opportunities to grow and learn. - Elaborating and processing the stressful event through the confrontation of the problematic situation. - Promoting personal growth.	- Psychoeducation on the positive contribution of problems. - The Book of Life: Confrontation. - Development of personal strengths.
5. Changing the meaning of problems.	- Elaborating and processing the stressful event through the development of a new meaning for the problematic situation. - Developing a new attitude towards problems.	- Elaboration of a new metaphorical meaning for the stressful event. - The Book of Life: Change the meaning. - Letter of projection towards the future. - Choice of a personal life motto.
6. Relapse prevention.	- Assessing achievements accomplished so far. - Reviewing of leaned techniques. - Identifying problematic situations an developing a plan to deal with them.	- Review of the therapeutic achievements. - Action plan to deal with future problems.

All the modules present the same structure: 1) module agenda; 2) therapeutic contents of the module; 3) exercises and activities to put the psychological techniques learned in the module into practice; 4) assessment of the knowledge acquired during the module; 5) tasks to be completed before advancing to the next module; and 6) summary of the module. An effort was made to simplify the language used in TAO to make it easily understood by users, regardless of their socio-demographic features. Regarding the ease of use of TAO, preliminary results obtained in an acceptance and usability study performed with clinical psychologists and patients with AjD showed that the program interface is highly intuitive and user-friendly and does not require any previous training [44].

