### Assessment

Measurements will be taken at five different moments: baseline, post-intervention, and three follow-up periods (3-, 6- and 12-month). The diagnostic interviews will be administered by a trained clinician by phone. Moreover, all interviewers engaged in the assessment of potential participants will be supervised by a clinical team composed of mental health professionals with extensive experience in the diagnosis and treatment of stress-related disorders. Questionnaires will be self-administered online via the same virtual platform as the intervention program. Table 2 provides an overview of the measures used at each time point.

**Table 2 Tab2:** Study measures and assessment times

Assessment moment	Telephone assessment performed by a therapist	Automatic online assessment
BL	Diagnostic Interview for Adjustment Disorders, ADIS-IV-L*	BDI, Suicide item, BAI, ISL, PTGI, PANAS, MQLI
Post-M	–	Post-module assessment scale, suicide item
Post-M1	–	Post-module assessment scale, suicide item, Expectation of treatment scale
Post-T	Diagnostic Interview for Adjustment Disorders	BDI, Suicide item, BAI, ISL, PTGI, PANAS, MQLI, Opinion of treatment scale
FU	Diagnostic Interview for Adjustment Disorders	BDI, Suicide item, BAI, ISL, PTGI, PANAS, MQLI

*BL,* Baseline; *Post-M,* post-module; *Post-M1,* post-module 1; *Post-T,* post-treatment; *FU*, follow-ups; *ADIS-IV-L,* Anxiety Disorders Interview Schedule for DSM-IV: Lifetime Version; *BDI,* Beck Depression Inventory - Second Edition*; BAI,* Beck Anxiety Inventory; *ISL,* Inventory of Stress and Loss; *PTGI,* Posttraumatic Growth Inventory; *PANAS,* Positive and Negative Affect Scale; *MQLI,* Multidimensional Quality of Life Questionnaire; *** used only when differential diagnosis is needed

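### In the TAO arm the suicide item is asked during treatment only when a self-paced module is finished, so a participant who stalls is not scheduled to be asked again until post-treatment

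*Protocol article*

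**What the plan says.** The Suicidal risk section gives two sources of information. The Diagnostic Interview for Adjustment Disorders, held by phone, covers suicidal thoughts. A separate online item is repeated over time: "The inclusion of a suicide item after each program module", then at post-intervention and at the follow-ups. The section says this "will make it possible to detect participants who are at risk of suicide during the intervention and once the intervention is over".

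Table 2 (Assessment) matches this and adds the item at baseline. Its post-module row reads "Post-module assessment scale, suicide item" in the online column, and the column headed "Telephone assessment performed by a therapist" holds a dash in both post-module rows. The Diagnostic Interview appears only at baseline, post-treatment and follow-up.

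On pace, the section on TAO describes seven sequential modules and says that "it takes about 7 to 10 weeks to complete it". One module a week is encouraged, but "everyone should progress at their own pace". Each module includes "tasks to be completed before advancing to the next module".

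The Support section gives the weekly call three aims: answering questions about using the program, encouraging continued work, and acknowledging progress. Calls last at most 10 minutes, number up to 10 over 7 to 10 weeks, and add no clinical content.

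**The concern.** The in-treatment check depends on progress, not on the calendar. A participant who keeps finishing modules is asked often. One who stops is not asked at all, because the event that triggers the question no longer occurs. Neither the weekly call aims nor any other stated procedure provides a substitute.

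The protocol itself gives reasons to care. The Background says that adjustment disorder may raise the risk of suicidal thoughts and behaviour. The Discussion says that reprocessing the stressful event can be very stressful for some patients. Table 1 places that work in modules 3 to 5; module 3, for example, aims at "Elaborating and processing the stressful event through the acceptance of the problematic situation". Stalling is also foreseen, since the Discussion cites about 30% non-completion for internet-delivered CBT. A participant who halts in the demanding modules would go unasked while still in the treatment period.

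What is at stake is patient safety and the accuracy of the detection statement. Randomisation, power and the primary comparison are not affected.

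**Working it through.** The plan states no figure on this point, so there is none to reproduce. The check has two parts: reading the schedule, and sizing the gap.

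**Reading the schedule (TAO arm, baseline to post-treatment)**

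| Possible occasion | Suicide question stated? | Source |
|---|---|---|
| Completion of a module | Yes, online item | Suicidal risk; Table 2 |
| Diagnostic Interview by phone | Not held in this interval | Table 2 |
| Weekly support call | None among the three aims | Support |
| Fixed calendar date | None | Assessment; Table 2 |

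Module completion is the only trigger. No deadline for finishing a module is stated.

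**Inputs for the size of the gap**

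- Seven modules, numbered 0 to 6 (Table 1), each followed by the item (Table 2).
- Post-treatment week T = 7 or 10. This is an assumption taken from the stated duration of TAO; the article does not date post-treatment for a participant who has stalled.
- One module per week before the stall. This is an assumption, equal to the encouraged pace.
- k = modules completed before the stall, so a stall in module k means modules 0 to k − 1 are done.

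**Weeks without the item = T − k**

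| Stall in module | k | T = 7 | T = 10 |
|---|---|---|---|
| 0 | 0 | 7 | 10 |
| 1 | 1 | 6 | 9 |
| 2 | 2 | 5 | 8 |
| 3 | 3 | 4 | 7 |
| 4 | 4 | 3 | 6 |
| 5 | 5 | 2 | 5 |
| 6 | 6 | 1 | 4 |

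Over the reprocessing modules 3 to 5, the smallest gap is 7 − 5 = 2 weeks and the largest is 10 − 3 = 7 weeks.

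**Times the item is asked, baseline to post-treatment inclusive**

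- Completer: 1 + 7 + 1 = 9.
- Stall in module 5: 1 + 5 + 1 = 7.
- Stall in module 3: 1 + 3 + 1 = 5.

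**How many participants**

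Applying the cited non-completion rate to the planned arm gives 0.30 × 34 = 10.2, or about 10. This is an upper-end illustration only: the rate is a general one for internet-delivered CBT, and the article does not say at which module non-completers stop.

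The gaps assume that the post-treatment assessment takes place. The Data analyses section expects some participants to miss it, and they would not be asked even then.

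**The case against.** The strongest reply is that this is a condensed article. It refers to a therapist handbook and to caller training, neither of which is shown, and either could contain a risk question. Three listed aims are not a full call script. The rule against added clinical content limits what patients are given and does not stop a caller from asking. The detection sentence can also be read as enabling rather than as a promise of weekly coverage.

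Several details deserve credit. Table 2 lists formal assessments and omits the support calls altogether, so its dash shows only that no telephone assessment is scheduled at post-module points; it does not show what is said in calls. The article describes tasks to be done before moving on, not a technical lock. The 2-to-7-week range rests on assumed timing. People at risk of suicide are excluded at entry, the linear format is meant to prepare users for the harder work, and experienced psychologists telephone weekly, so a stalled participant is not without contact and may be recognised informally. The waiting list has no item during its 7 weeks either.

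These points limit the size of the concern but do not remove it. It does not rest on a missing safety procedure: the article positively states when the item is asked and what the calls are for, and a team following both would leave a stalled participant unasked. Exclusion at entry does not cover risk that emerges later, which the plan recognises by repeating the item. The waiting list is not doing the reprocessing work, and the detection statement concerns the intervention.

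**Conclusion.** The concern holds. As written, the suicide item in the TAO arm between baseline and post-treatment depends solely on finishing modules, and the stated call aims do not fill the gap. The statement about detecting risk during the intervention is therefore true only of participants who keep completing modules.

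A stall in modules 3 to 5 leaves 2 to 7 weeks unasked, and a stall at the very start up to 10. Both figures assume one module per week beforehand and post-treatment at week 7 to 10. The number of people affected is unknown. This should be fixed because the consequence is a safety one and the remedy is cheap. Confidence is medium, since an unseen call manual might already contain the question.

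**What to change.** Add a fourth aim to the weekly call in the Support section: in any week in which the suicide item was not answered online, the caller asks it. The call should carry the change because someone who has stopped logging in may never see an online prompt; a weekly online prompt can supplement it. Add a telephone entry for the treatment weeks to Table 2, and a matching sentence under Suicidal risk. The post-module scale can stay as it is. A single screening question is assessment, not therapy, so it does not breach the rule on clinical content. What follows a positive answer is for the clinical team to settle.

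The cost is three small text edits, with no new staff, instrument, visit or call. Extra askings per participant are at most T minus modules completed:

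- one module per week: 7 − 7 = 0;
- all modules over 10 weeks: 10 − 7 = 3;
- stall in module 5: 2 to 5; stall in module 3: 4 to 7;
- worst case: 10 − 0 = 10, equal to the maximum number of calls already planned.

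The downsides are some additional alerts for the clinical team, continued non-coverage of anyone who does not answer the phone, and slightly closer monitoring of TAO than of the waiting list.

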#### Other post-module measures recorded by the system

The post-module assessment will be performed using a short scale developed by the clinical team involved in the present trial. In addition to suicidal risk, the following variables will also be assessed: the general mood using a 7-point face rating scale, and the intensity of several emotions (joy, sadness, anger, hope, anxiety, relaxation, pride, and guilt) on a 7-point numeric scale. Finally, 10-point numeric scales will explore: (1) the feeling of self-efficacy to deal with the stressful event that caused the AjD; (2) acceptance of negative events; (3) openness to new experiences; and (4) satisfaction with the TAO module.

### Data analyses

The statistical package IBM SPSS Statistics version 22.0 for Windows will be used for data analyses. Baseline differences between groups will be explored for continuous and categorical measures using both t-tests and chi-square tests. Repeated-measures ANOVAs will be used to assess within-group changes over time in primary and secondary outcome measures. Effect sizes will be estimated using Cohen’s d. Linear regression models will be used to study the effect of different variables (e.g., gender, age, and treatment expectations) on adherence and response to the intervention. Any participants who do not complete the post-intervention assessment will be considered drop-outs. On the other hand, the number of times each patient uses the program will be used as the measure of adherence.

Before analyzing the data, a review of state-of-the-art analytic methodology for RCT will be carried out in order to ensure the use of the most suitable statistical analyses. Finally, following SPIRIT and CONSORT guideline recommendations, both intention-to-treat and per-protocol analyses will be reported [34, 36].

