### Sample size

The sample size for the trial was calculated following the method described by Campbell, Julious, and Altman [37], and Freiman, Chalmers, Smith, and Kuebler [38]. G*Power 3 software [39] was used to facilitate power analysis.

Because there is no published research on the effectiveness of ICBT for the treatment of AjD, the sample size was calculated taking into account outcomes found in trials that used the BAI and BDI-II as measures of clinical change after an ICBT intervention in patients with clinical depression or anxiety disorder [40–42]. After reviewing the literature and adopting a more conservative approach, an effect size of .70 was assumed in the present study. Considering a significance level of 5% and a power of 80%, 26 participants in each group would be enough to detect the assumed difference. However, because the literature reveals dropout rates from ICBTs of around 30% [43], a sample of 68 participants will be recruited (34 per group).

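### Baseline is tested between the randomised arms, and the only outcome method named has no baseline covariate; prespecified baseline adjustment would be more precise at no cost in data

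*Protocol article*

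**What the plan says.** All of the relevant analysis text is in the Data analyses section of the Protocol article.

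- Baseline: "Baseline differences between groups will be explored for continuous and categorical measures using both t-tests and chi-square tests". The section does not say what will follow from the results.
- Outcomes: "Repeated-measures ANOVAs will be used to assess within-group changes over time in primary and secondary outcome measures". Baseline enters as one level of time. No covariate is named.
- Regression: "Linear regression models will be used to study the effect of different variables (e.g., gender, age, and treatment expectations) on adherence and response". These models look for predictors; the baseline score is not among the examples, and no adjusted arm comparison is described.
- Room for revision: before the data are analysed, "a review of state-of-the-art analytic methodology for RCT will be carried out in order to ensure the use of the most suitable statistical analyses".

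The Randomization and blinding section describes blocked randomisation from a computer-generated sequence. Table 2 (Assessment) shows BDI-II, BAI and every secondary scale collected at baseline and again post-treatment. The Sample size section says that "an effect size of .70 was assumed in the present study", sets recruitment at 34 per group and expects about 30% dropout. The waiting-list section offers controls the programme after their second assessment, so the post assessment is the only point at which the randomised arms can be compared untreated against treated.

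**The concern.** Because allocation is random, any baseline difference between the arms is due to chance. A significance test asks whether it is, and the answer is known beforehand. A non-significant result does not show that the arms are alike on a prognostic score, and a significant one does not show that the randomisation failed. What matters for the treatment estimate is the size of the imbalance and how strongly baseline predicts outcome; the p-value measures neither.

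The baseline scores have a better use. Adjusting the post comparison for the same scale's baseline removes the effect of chance imbalance and reduces residual variance. The trial is small and expects substantial dropout, so this precision matters. The method that is named uses baseline only as a repeated measurement. If it is turned into a comparison of arms by way of the group-by-time interaction, it handles baseline less efficiently than a covariate would.

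**Working it through.** **Inputs.** From the Sample size section: d = 0.70, 5% significance, 34 recruited per arm, 30% dropout. Completers per arm: 34 x 0.7 = 23.8, taken as 24. From Table 2: seven baseline scale scores (BDI-II, BAI, ISL, PTGI, positive affect, negative affect, MQLI). Assumed: the baseline-to-post correlation r, which the document does not give (0.3 to 0.8 shown); equal SD at baseline and post; two-sided testing.

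**The plan's own figure.** The stated 26 per group is reproduced by an unadjusted two-group comparison of means at one-sided 5% (exact t power 80.1%). At two-sided 5% the same 26 give 69.7%, and 34 are needed. Recruitment of 34 follows from 26 x 1.3 = 33.8. Sidedness and dropout inflation are separate matters; the relevant point here is that the calculation takes no credit for baseline adjustment.

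**What the baseline tests can detect.** The smallest difference reaching p<0.05 at 34 per arm is t(0.975, 66 df) x sqrt(2/34) = 0.484 SD. The chance imbalance on one scale has SD sqrt(2/34) = 0.243, so (normal approximation):

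- P(imbalance of 0.3 SD or more, either direction) = 21.6%.
- P(imbalance between 0.3 and 0.484 SD) = 17.0%. These would be reported as not significant.
- P(at least one of seven scales significant) = 1 - 0.95^7 = 30.2% if the scales were independent. They probably overlap, so this is only a guide.

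**What a change-score contrast does with an imbalance.** With two time points, group-by-time in a repeated-measures ANOVA is the t-test on change. Given a baseline imbalance delta, the expected post difference shifts by r x delta. Subtracting baseline removes the whole of delta, leaving an error of (1-r) x delta in the opposite direction. ANCOVA subtracts r x delta and leaves none.

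| r | error for delta = 0.3 SD | error for delta = 0.484 SD |
|---|---|---|
| 0.3 | 0.21 SD | 0.34 SD |
| 0.5 | 0.15 SD | 0.24 SD |
| 0.7 | 0.09 SD | 0.15 SD |
| 0.8 | 0.06 SD | 0.10 SD |

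At r = 0.5, an imbalance at the edge of significance moves the estimate by 0.24/0.70 = 34% of the assumed effect.

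**Power.** Standardised effect for change: d/sqrt(2(1-r)), with 2n-2 df. For ANCOVA: d/sqrt(1-r^2), with 2n-3 df. Power is from the noncentral t, two-sided 5%, n = 24 per arm. The post-only comparison has 66.1% power whatever r is.

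| r | effect, change | effect, ANCOVA | power, change | power, ANCOVA | gain (points) |
|---|---|---|---|---|---|
| 0.3 | 0.592 | 0.734 | 51.9% | 70.1% | 18.2 |
| 0.5 | 0.700 | 0.808 | 66.1% | 78.2% | 12.1 |
| 0.7 | 0.904 | 0.980 | 86.5% | 91.3% | 4.8 |
| 0.8 | 1.107 | 1.167 | 96.4% | 97.7% | 1.3 |

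The variance ratio, ANCOVA to change score, is (1-r^2)/(2(1-r)) = (1+r)/2, which is 0.65 at r = 0.3 and 0.90 at r = 0.8. It is below 1 for every r below 1. For r below 0.5 the change score does worse than ignoring baseline altogether.

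**The case against.** Four points can be made for the plan.

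1. *The tests are nearly harmless as stated.* A reader might infer that they stand in for adjustment, or that a non-significant result will be offered as proof that the arms are comparable. The text says neither; the differences are only to be explored, and nothing is said to depend on the result. This stands. False reassurance is a risk of the practice and is not something the plan commits to. Dropping the tests alone would change little.

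2. *This is a condensed article, covariates are commonly left to an analysis plan, and a methodology review is promised.* The silence on covariates would be no finding by itself. But the article does name methods: tests for baseline and an ANOVA without a covariate for outcomes. The review makes it possible that the final model will differ, but it fixes no adjustment, and it leaves the choice open until shortly before analysis.

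3. *Baseline is already in the ANOVA.* A reader might infer that an imbalance passes straight into the comparison. That would describe a post-only analysis, which is not what is planned. A change score removes the imbalance and overshoots by (1-r) of it. The fault is over-correction and lost precision.

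4. *The group-by-time contrast is itself inferred.* The ANOVA sentence speaks only of within-group change. This stands too, so the power comparison is conditional on that reading. It is the natural way to get an arm comparison from the named method, but the document does not state it.

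The size also depends on r. At r = 0.8 the gain is about one point.

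**Conclusion.** The point holds in a limited form. The baseline significance tests cannot inform the treatment comparison, and at 34 per arm they pass over imbalances of up to about 0.48 SD. The one outcome method named does not use baseline as a covariate. Read as a between-arm change-score contrast, it mis-corrects a chance imbalance by (1-r) of its size and gives up between about 18 points of power (r = 0.3) and about 1 point (r = 0.8) against ANCOVA, with 12 points at r = 0.5. These figures assume d = 0.70, 24 completers per arm, two-sided 5%, equal SDs and a correlation that the document does not supply. The direction does not depend on r, but the size does.

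The documents do not support saying that the tests replace adjustment, that they will be used to claim comparability, or that the imbalance is left untouched in the comparison. This is a worthwhile improvement to a stated method; it does not show that the trial's result would be invalid.

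**What to change.** In the Data analyses section:

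- Replace the baseline t-tests and chi-square tests with a description of baseline characteristics by arm, without p-values.
- State that the between-arm comparison of BDI-II and of BAI at the post assessment is adjusted for the baseline score of the same scale, by ANCOVA or by a mixed model with baseline as a covariate, whatever imbalance is observed. Say the same for each secondary scale.
- Fix this before any outcome data are examined, so that the planned methodology review cannot make the adjustment depend on the data.

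The cost is analysis wording only. Baseline scores on every scale are already collected, the named software can fit either model, and neither the sample size nor the assessment schedule has to change.
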